### Monitoring and quality assurance

The adverse events to be recorded are infection (any diagnosis of infection resulting in any treatment); re-operation (including reason for reoperation); death (including cause and likelihood of any casual link between treatment or study participation and death) and implant failure (fracture or migration of implants).

Data will be collected by local site investigators and submitted securely to the project manager at the administering institution. Data will be stored in locked filing cabinets and password protected computers within the administering institution. The coordinating and principal investigators are responsible for the adherence to all ethical committee rules and guidelines for the accuracy and completeness of all forms, entries and informed consent.

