**Methods/Design:**

SOFIE is an international study with a multicentre pragmatic randomised controlled trial design. The primary objective of the study is to compare a patient related outcome, the Disability of the Arm Shoulder and Hand (DASH) Score, between patients treated operatively and non-operatively at twelve months.

Patients will be considered for the study if they are 75 years of age or older, medically fit for surgery, have an isolated displaced olecranon fracture, and present within 14 days of injury. Eligible patients willing to participate will be randomised either to operative fixation, with surgery using the preferred technique of the treating orthopaedic surgeon (tension band wiring or plate fixation), or to non-operative treatment involving early range of motion as tolerated.

Secondary outcome measures will include pain, active range of motion, elbow extension strength, and any adverse events (infection, secondary interventions) at 3 and 12 months.

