## Background

The incidence of olecranon fractures in the adult population is 11.5 per 100,000 per year. These fractures make up 20 % of all proximal forearm fractures, and 8–10 % of all elbow fractures. Recent studies have reported an increasing incidence of olecranon fractures in the elderly population [1, 2]. In this age group, they are predominantly fragility fractures seen in patients with multiple co-morbidities and low functional demands [3, 4].

The current standard treatment for displaced olecranon fractures, based on case series and tradition, is operative fixation with either tension band wiring or plate fixation [5–10]. Despite being commonly performed, the results from studies investigating outcomes and complications after operative fixation are conflicting, especially in the elderly with osteoporotic bone. Reported complications include those related to anaesthesia, as well as those specific to the surgical fixation (wire migration, soft- tissue irritation, olecranon bursitis, wire breakage, fracture displacement and the need for a second operation for removal of hardware, with rates as high as 70 %) [11–16].

Further to this high complication rate, there is recent evidence from case series that non-operative management of displaced olecranon fractures is a reasonable option in elderly patients, with comparable outcomes without the risk of anaesthetic and surgical complications [10, 17–19].

Despite extensive case series data, we are unaware of any study directly comparing operative and non-operative management of displaced olecranon fractures in the elderly. The aim of our study is to perform a randomized control trial testing for superiority of operative treatment over non-operative treatment in restoring upper limb function for displaced olecranon fractures in the elderly.

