### Outcome measures

Participants will be followed up at two weeks, three months and twelve months post intervention. The primary outcome will be the Disability of the Arm Shoulder and Hand (DASH) Score at 12 months [20]. The DASH score is a widely used, validated outcome tool used in studies of upper limb injuries and surgery, and is a continuous score on a scale from 0 to 100 [21]. Secondary outcome measures collected at 3 months and 12 months will include DASH, EuroQol Visual Analogue Score (EQ VAS), Pain Visual Analgoue Scale (VAS), Mayo Elbow Performance Score (MEPS), complications, elbow active range of motion, and elbow extension strength.

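### The adverse-event list counts re-operation, which read literally leaves out a first operation in the non-operative arm and does not match the wider terms used elsewhere in the article

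*Protocol article*

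**What the plan says.** Three places in the protocol article describe the harms to be collected, in different terms.

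- **Monitoring and quality assurance** introduces a list with "The adverse events to be recorded are infection (any diagnosis of infection resulting in any treatment"). It continues with "re-operation (including reason for reoperation"), death, and "implant failure (fracture or migration of implants"). Nothing in the sentence marks the four items as examples.
- **Abstract, Methods/Design** includes among the secondary outcomes "any adverse events (infection, secondary interventions) at 3 and 12 months".
- **Outcome measures** lists, at 3 and 12 months, "Mayo Elbow Performance Score (MEPS), complications, elbow active range of motion, and elbow extension strength". Complications are not defined there, and nothing links them to the monitoring list.

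The Background shows why harms matter to this comparison. It credits non-operative care, on case-series evidence, with "comparable outcomes without the risk of anaesthetic and surgical complications".

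**The concern.** Surgery during follow-up is an informative event in both arms. In the operative arm it is typically hardware removal or revision. In the non-operative arm it is a first fixation after the allocated treatment has not sufficed. The word re-operation covers the former but, taken literally, not the latter. If sites apply the list as worded, one arm's later surgery is counted and the other's is not.

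The wording carries weight because the interpretation falls to people who know the allocation. The Interventions section says that investigators are not blinded, and the monitoring section has local site investigators collect the data. One site may enter a first fixation as a re-operation and another may not. At stake is a secondary outcome that bears on the trial's rationale. The primary outcome is not at stake.

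**Working it through.** **Step 1: the terms side by side.**

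| Event | Monitoring list, read literally | Abstract: secondary interventions | Outcome measures: complications |
|---|---|---|---|
| Second operation, operative arm | counted | counted | undefined |
| First operation, non-operative arm | not named | naturally covered | undefined |
| Implant migration or breakage | counted as implant failure | not addressed | undefined |
| Hardware removal | counted as re-operation | counted | undefined |

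The second row is where the monitoring list and the abstract part. The third column of terms cannot settle it, because it has no definition.

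**Step 2: number of patients.** The article disputes nothing here, but the arm size is needed. The plan's figures are 26 per group at 12 months and 20% loss: 2 × 26 = 52, and 52 / 0.80 = 65, as stated. The standard deviation is not given. Solving for it with a 15-point difference, two-sided 0.05 and 95% power gives about 15.0, so the sample size reproduces on that assumption (normal approximation). The arm size at randomisation is 65 / 2 = 32.5, taken below as about 32.

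**Step 3: effect of the literal reading.** Let p_o be the proportion of the operative arm with a re-operation, and p_n the proportion of the non-operative arm with a first operation.

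- Difference under the literal list: p_o − 0 = p_o
- Difference under an arm-neutral rule: p_o − p_n
- Discrepancy: p_o − (p_o − p_n) = p_n

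For this one item the discrepancy always runs against the operative arm and equals p_n. The documents give no value for p_n, so all the rates below are assumptions.

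| Assumed p_o (events in 32) | Literal difference | p_n = 0% (0) | p_n = 5% (1.6) | p_n = 10% (3.2) | p_n = 20% (6.4) |
|---|---|---|---|---|---|
| 10% (3.2) | 10 | 10 | 5 | 0 | −10 |
| 20% (6.4) | 20 | 20 | 15 | 10 | 0 |
| 40% (12.8) | 40 | 40 | 35 | 30 | 20 |

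Differences are in percentage points, operative minus non-operative. The last four columns give the arm-neutral difference; expected events in the non-operative arm are in brackets in the column heads. With arms of this size, about three first operations move the comparison by 10 points. If no first operations occur, the wording makes no difference.

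**The case against.** The strongest reply is that the list belongs to safety monitoring and does not define the comparative outcome. Outcome measures names complications separately and does not restrict them to four events, and the abstract's term already takes in a first fixation. The article is also a condensed account: the full protocol is not shown, and the data form may already hold an arm-neutral item. This stands to the extent that the documents do not prove any event will go uncounted. It does not remove the point, because the monitoring sentence is a positive statement of what will be recorded and is narrower than the abstract's.

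A reader might infer several stronger things that the documents do not support.

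- *That failures of non-operative care are concealed.* The Statistical analysis section plans an as-treated analysis, which needs the treatment actually received. Crossover to surgery should therefore be known, even if it is not labelled an adverse event.
- *That function cannot be weighed against harm.* Infection, death, re-operation, implant failure, complications, pain and function are all collected.
- *That the 70% in the Background measures unrecorded harm.* That figure attaches most directly to second operations for hardware removal, which the list does record.
- *That most of the Background's surgical harms are missed.* Migration and breakage fall under implant failure, and irritation or bursitis leading to a second operation is recorded through its reason. What is unnamed is mainly non-fatal anaesthetic events, and soft-tissue or displacement events that do not lead to surgery. Itemising these is detail an article may leave to the full protocol.
- *That listing implant failure is itself unfair.* It is a genuine harm specific to surgery and belongs on the list.

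**Conclusion.** The point holds as an inconsistency with a practical consequence. The monitoring list, applied as worded, counts later surgery in the operative arm but not a first operation in the non-operative arm, and it conflicts with the abstract's arm-neutral term. The undefined complications outcome does not resolve the conflict.

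The conclusion rests on reading re-operation literally and on the list being used for the between-arm comparison; the article confirms neither use nor non-use. The discrepancy equals the proportion of non-operative patients who have a first operation. The documents give no such rate, so the size cannot be stated; over assumed rates of 0% to 20% it is 0 to 20 percentage points. The direction is known for this item only, and no claim is made about the net direction across all harms. The primary DASH comparison and the sample size do not change. This should be corrected, but it does not threaten the trial's main result.

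**What to change.** Reconcile the abstract, Outcome measures, and Monitoring and quality assurance. Replace the re-operation item with: any surgery to the injured elbow after the initial allocated treatment, including first fixation in a patient allocated to non-operative care, with date and reason. Record it identically in both arms from randomisation and report it by allocated group. The planned initial fixation in the operative arm is the allocated treatment and is not an event. State whether the complications outcome consists of the monitoring list or is wider.

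Optionally, state that complications also include the non-fatal anaesthetic and soft-tissue events cited in the Background when they are noted at existing visits. No extra imaging is proposed, and recording of further displacement is not asked for: the article mentions radiographs only for eligibility, so that could add cost.

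The cost is one reworded item and a few additional form fields, with no change to visits, the primary analysis or the sample size.

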## Discussion

There are no prospective randomised controlled trials comparing operative and non operative treatment for displaced olecranon fractures in the elderly, with current management based on case series and tradition alone. The SOFIE trial will compare the management of these fractures and in addition to examining a previously unanswered clinical question about the effectiveness of a commonly performed orthopaedic procedure, this study will guide future treatment for this common injury, potentially changing current practice.

## Abbreviations

AP: anteroposterior
DASH: disability of the arm shoulder and hand score
EQ VAS: EuroQol visual analogue scale
VAS: visual analogue scale
MEPS: Mayo elbow performance score
